**Methods:**

Patients with unresectable locally and or regionally advanced pathologically confirmed cSCC (stage III-IVa) deemed fit for CRIO by consensus of the Multidisciplinary meeting will be eligible. In the first stage of a two-stage minimax design, we aim to recruit a total of 15 patients. If fewer than 7 patients achieved a complete response in the first stage, we will conclude the treatment is not more effective than standard treatment. The co-primary endpoints of CRIO are the safety of treatment (acute and late toxicities) and the rate of complete response. Secondary endpoints would include overall survival, progression free survival, and locoregional control. Translational research endpoints including biomarkers (CD73, CD39, PD-1, PD-L1) will also be explored utilising multiplex immunohistochemistry on tumour biopsy samples obtained prior to commencing treatment and during treatment (week 2). In addition, the utility of CXCR-4 PET/CT scan will be explored.

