#### Intervention description

Chemotherapy Platinum-based chemotherapy will commence on either day 1–3 of the radiation and preferably repeated on the same day of each week. A maximum of 7 weekly doses will be given. In cases where the chemotherapy is delayed or ceased, the radiotherapy will continue according to protocol. The primary chemotherapy regimen is cisplatin 40 mg/m^2^/week. Carboplatin may be used for patients with renal or cardiac or hearing impairment, at the discretion of the treating physician. Full blood counts, ELFT, magnesium, and renal function tests must be performed within 48 h prior to each weekly chemotherapy dose.

2.Immunotherapy Durvalumab will be supplied by AstraZeneca as a 500-mg vial solution for infusion after dilution. The solution contains 50 mg/mL durvalumab, 26 mM histidine/histidine hydrochloride, 275 mM trehalose dihydrate, and 0.02% weight/volume (w/v) polysorbate 80; it has a pH of 6.0. The nominal fill volume is 10.0 mL. Investigational product vials are stored at 2 to 8 °C (36 to 46°F) and must not be frozen. Drug products should be kept in secondary packaging until use to prevent excessive light exposure.Concurrent phase: administered every 4 weeks during chemoradiation (weeks 1 and 5).Adjuvant phase: same dose and frequency as concurrent phase in weeks 9,13 and 17. Up to 6 additional doses until the final disease status can be determined on PET/CT. Patients who achieve complete response or progressive disease will discontinue durvalumab immediately. Patients who undergo salvage surgery for residual disease will receive 6 more doses of durvalumab after surgery.Fixed dosing of 1500 mg every 4 weeks (approximate 20 mg/kg every 4 weeks)

3.Radiotherapy Intensity Modulated Radiotherapy (IMRT) should be utilised on all patients in the study cohort.

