### Outcomes

#### Primary outcome

To assess the safety of CRIO-incidence of treatment related toxicities
All treatment related toxicities will be recorded at each clinic visit for a total of two years in the Case Report Form using the CTCAE 4.03.To assess the rate of complete response

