**Fig. 1 Fig1:**
[figure not shown]
Consort diagram of CRIO trial

Patients who do not achieve a CR should be considered for salvage surgery. Patients who achieve CR after such surgery will be designated CR (Su) and will undergo follow up as above. Patients with residual disease which is unresectable will be recorded as having a treatment failure.

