##### Patients with large nerve perineural spread

These patients are not eligible for assessment of complete response and will be assessed as progression-free or not based on symptoms and/or image findings. Clinical follow-up should occur as above. The first progress MRI should be performed at 3 months from completion of treatment and then 6 monthly thereafter.

Once a CR has been declared, patients should cease the Durvalumab and clinical follow-up at four weekly intervals for a total of 1 year from the start of treatment. The follow up schedule can be found in Table 1. Physical examination will include direct inspection and palpation of accessible sites. Imaging will be done if there is clinical suspicion of recurrence or progression. Biopsy or cytological confirmation of recurrent disease should be obtained whenever possible. The clinician will record disease status, sites and dates of any relapse and late effects of treatment.

**Table 1 Tab1:** Schedule of assessments

Investigation	Screening /Baseline	Wk 1	Wk2	Wk3	Wk4	Wk5	Wk6	Wk7	Wk9	Wk13	Wk17	Wk 19	Wk 21, 25, 29, 33, 37, 41	Wk 27	Months post treatment 2,4,6,8,10,12,15,18,21,24,30,36,42,48,54,60
Informed consent	x														
Histological confirmation of SCC	x														
Repeat biopsy (skin or lymph nodes]			× ^1^												
Medical history	x^6^														
Physical examination (ECOG, vital signs, toxicity]	x^6^	x	x	x	x	x	x	x	x	x	x		x		x
Concomitant meds	x														
Urine analysis	x														
Pregnancy test	x^6^														
FBC	x^6^	x	x	x	x	x	x	x	x	x	x		x		x^4^
U&E, LFT’s	x^6^	x	x	x	x	x	x	x	x	x	x		x		x^4^
Coagulation profile, TSH, hep, HIV															
x															
FDG PET	x^7^											x		x^2^	
CXCR4 PET /CT	x^3^			x											
Contrast CT / MRI	x^7^											x^4^			
Disease status		x	x	x	x	x	x	x	x	x	x		x		x
Blood	x			x						x			x^5^		

^1^Not mandatory

^2^If week 19 FDG PET is equivocal

^3^Pretreatment

^4^If clinically indicated

^5^Weeks 21 and 37 only

^6^Due within 14 days of trial registration

^7^Due within 28 days of trial registration

Patients who are considered treatment failures will be followed at the above time points for survival only. This may be done at clinic visits when seen for ongoing treatment or by telephone call

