### Definition of treatment failure

The patient will be considered as having treatment failure if:Progressive disease at any time;Residual disease at 12 weeks and not amenable to salvage surgery;Recurrent disease within the irradiated field during follow up that is biopsy-proven or increases over serial imaging/clinical examination;Metastatic disease

Secondary Outcomes include overall Survival, progression free survival, and locoregional control will be assessed.

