### Data collection and management

#### Plans for assessment and collection of outcomes

As per schedule of assessments (Table 1). All treatment related toxicities will be recorded at each clinic visit for a total of two years in the Case Report Form using the CTCAE 4.03. (https://evs.nci.nih.gov/ftp1/CTCAE/CTCAE_4.03_2010-06-14_QuickReference_8.5x11.pdf).

Disease status of patients will be recorded at each visit during and after completion of treatment.

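### Toxicity recording ends at treatment failure, although late toxicity is co-primary and is to be recorded for two years

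*Protocol article*

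**What the plan says.** The Abstract (Methods) sets the endpoints: "The co-primary endpoints of CRIO are the safety of treatment (acute and late toxicities) and the rate of complete response". The Primary outcome section sets the recording period: "All treatment related toxicities will be recorded at each clinic visit for a total of two years". The section on plans for assessment and collection of outcomes repeats it: "All treatment related toxicities will be recorded at each clinic visit for a total of two years in the Case Report Form". Neither makes an exception for patients whose treatment has failed. Table 1 lists toxicity as part of the physical examination at weeks 21 to 41 and at the post-treatment visits.

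The sentence below Table 1 then sets a different rule for one group: "Patients who are considered treatment failures will be followed at the above time points for survival only". It adds that the contact may be a telephone call.

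Failure is defined broadly. Under Definition of treatment failure it covers progression at any time, in-field recurrence, metastatic disease, and "Residual disease at 12 weeks and not amenable to salvage surgery". The text below Figure 1 agrees: "Patients with residual disease which is unresectable will be recorded as having a treatment failure".

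The Intervention description gives durvalumab at weeks 1, 5, 9, 13 and 17, then "Up to 6 additional doses until the final disease status can be determined on PET/CT". It also states: "Patients who achieve complete response or progressive disease will discontinue durvalumab immediately".

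**The concern.** The two rules cannot both be followed for a patient who fails within two years. If sites follow the rule below Table 1, late toxicity is observed only while a patient is free of failure. Delayed immune-related events and late radiation effects can appear after that point.

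The regimen combines three treatments in a new way, and stage 1 has 15 patients, so each patient's late follow-up counts. Losing a few lowers the chance of seeing a late event at all. If failures also stay in the denominator, the reported late rate is too low. A later analysis plan cannot recover grades that were never collected.

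**Working it through.** **Does another section restore the recording?**

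- The section on discontinuing or modifying interventions says adverse events will be monitored systematically. The only routine review it schedules is before each chemotherapy or immunotherapy cycle, and durvalumab stops at progression.
- Permanent discontinuation of study treatment keeps patients who stop durvalumab in follow-up until progression, completion of study assessments or study closure. Progression is again an end point.
- Provisions for post-trial care sets visit frequency over five years and does not mention toxicity.
- Reporting of serious adverse events has no stated cut-off at failure, so serious events may still be caught.

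The gap is therefore in routine graded toxicity.

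**Timing.** Inputs: durvalumab at week 17 and four-weekly radiotherapy-independent dosing thereafter (Intervention description); a 7-week radiotherapy course (Target volumes and doses); response scan at week 19 ± 2, repeated at week 27 if equivocal (Patients with measurable disease).

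- Failure at week 19: 19 − 17 = 2 weeks after the last dose, and 19 − 7 = 12 weeks after radiotherapy.
- Failure at week 27, with additional doses at weeks 21 and 25 if the four-week schedule is kept: 27 − 25 = 2 weeks after the last dose, and 27 − 7 = 20 weeks after radiotherapy.
- The scan window puts a week 19 assessment 0 to 4 weeks after the week 17 dose. Progression at any time also allows a shorter gap.
- If the two years run from the start of treatment (assumption; the start is not stated), a week 19 failure loses 104 − 19 = 85 of 104 weeks, or 82%.

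**Number of failures.** The document gives none. Inputs: complete response rates of 50% and 70% and stage sizes of 15 and 28 (Sample size). Assumptions: half of the patients without complete response are salvaged by surgery, and failure occurs at about week 19.

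- Failure proportion: (1 − 0.70)/2 = 0.15 to (1 − 0.50)/2 = 0.25.
- Of 15: 15 × 0.15 = 2.25 to 15 × 0.25 = 3.75, about 2–4.
- Of 28: 28 × 0.15 = 4.2 to 28 × 0.25 = 7, about 4–7.
- With no salvage: 15 × 0.30 = 4.5 to 15 × 0.50 = 7.5, and 28 × 0.30 = 8.4 to 28 × 0.50 = 14.

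**Chance of seeing at least one case of a late toxicity with 10% risk**, 1 − 0.9^n, with n the number still observed:

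| Patients | All observed | Fewer failures | More failures |
|---|---|---|---|
| 15, half salvaged | n = 15: 0.794 | n = 13: 0.746 | n = 11: 0.686 |
| 28, half salvaged | n = 28: 0.948 | n = 24: 0.920 | n = 21: 0.891 |
| 15, none salvaged (failures rounded up to 5 and 8) | n = 15: 0.794 | n = 10: 0.651 | n = 7: 0.522 |

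**Reported rate for a true 30%**, if failures stay in the denominator and carry equal late risk (both assumptions), half salvaged:

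- 15 patients: 0.30 × 13/15 = 0.26 and 0.30 × 11/15 = 0.22.
- 28 patients: 0.30 × 24/28 = 0.257 and 0.30 × 21/28 = 0.225.

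**The case against.** The strongest reply is that the rule below Table 1 only thins the visit schedule. On that reading, toxicity would still be recorded whenever a failed patient attends clinic, and the loss would fall mainly on those followed by telephone. This is possible, but it sits badly with a rule that limits follow-up to survival. At best, sites face two instructions for a co-primary endpoint.

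Several other points stand in part:

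- The general statement on monitoring adverse events has no cut-off, and a committee reviews safety every six months. Neither gives a schedule for graded recording after failure.
- The full protocol may hold a reporting window after the last dose, and the toxicity denominator belongs in an analysis plan. Neither absence is counted against the article here. The downward bias in the reported rate is conditional for that reason.
- The salvage fraction has no source in the document. Patients are enrolled as unresectable, so salvage could be rarer and the loss larger. Patients with large nerve perineural spread are not assessed for complete response, so the planning rates do not apply to them, and those who stay progression-free remain in follow-up.
- The detection figures treat failures as contributing no late observation. A week 19 failure does contribute about 12 weeks after radiotherapy, and later failures contribute more. Early death among failures would also shrink the gap.
- Further therapy after failure makes attribution harder. That is a reason to record when it starts; it does not justify recording nothing.

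**Conclusion.** The concern holds. The follow-up rule for failures conflicts with the two-year recording of a co-primary endpoint, and following it loses graded late toxicity.

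The size is moderate. With the planning response rates and half of non-responders salvaged, detection of a 10% late toxicity drops by about 5 to 11 percentage points with 15 patients (79% to 69–75%) and by about 3 to 6 points with 28 (95% to 89–92%). Where failures stay in the denominator, a true 30% would read as about 22–26%. The timing follows directly from the dose and scan weeks; the patient numbers rest on assumptions.

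The complete response endpoint, the sample size and the error rates are untouched. This should be corrected, but it does not undermine the efficacy design.

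**What to change.** Change the sentence below Table 1 so that treatment failures are followed for survival and treatment-related toxicity to two years, with a fixed minimum toxicity period after the last durvalumab dose whatever the disease status. Record the date any new systemic therapy starts, and keep collecting late in-field radiation effects after it. When reporting, show the number still under toxicity observation at each time, or use cumulative incidence with death as a competing event; this part can be left to the analysis plan.

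The cost is one amended rule, a therapy-start date, and a toxicity form at contacts already scheduled for survival. The downsides are harder attribution once other therapy begins and weaker grading by telephone.

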### Definition of treatment failure

The patient will be considered as having treatment failure if:Progressive disease at any time;Residual disease at 12 weeks and not amenable to salvage surgery;Recurrent disease within the irradiated field during follow up that is biopsy-proven or increases over serial imaging/clinical examination;Metastatic disease

Secondary Outcomes include overall Survival, progression free survival, and locoregional control will be assessed.

### Participant timeline

A timeline of 2 years is used to accrue 15 patients. Please also see Table 1, schedule of assessments.

#### Sample size

A two-stage minimax design will be applied, which requires an initial sample of 15 patients, with possibly an additional 13 patients required (total 28) subject to feasibility. The hypothesis that the proportion responding is 70% or more compared to the alternative hypothesis that 50% or fewer respond will be tested using a two sided binomial test with a target significance level of 0.10 and power of 0.80. Fifteen patients would be recruited in the first stage and if 7 or fewer patients respond the trial will be terminated and we will conclude that the treatment is not more effective than standard treatment. If 8 or more patients respond, the trial may go to the second stage, recruiting a further 13 patients. Of the total of 28 patients, 18 or more must respond to the treatment to be considered better than current treatment. Sample size was calculated using the PASS 13 Power Analysis and Sample Size Software (NCSS, 2014).

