### Statistical methods

#### Statistical methods for primary and secondary outcomes

For the first stage, the analysis will focus on descriptive statistics. Categorical variables will be summarised using frequencies and percentages and continuous variables will be summarised using means with standard deviations or as medians with interquartile ranges. Median survival time (with 95% CI) will be described and survival time will be presented using a Kaplan–Meier curve. Safety/toxicity data will be presented according to the frequency of occurrence. The proportion of patients experiencing the primary outcome (complete response) will be presented with 95% confidence intervals and compared to the hypothesized null effect of 0.5 using an exact binomial test.

Secondary outcomes including overall survival, disease free survival, time to progression and loco-regional control will be presented using a Kaplan–Meier curve.

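### The Sample size section states a two-sided 0.10 test with the hypotheses reversed, but its 15/28 boundaries are a one-sided 0.10 design, so 18/28 succeeds by the rule and fails the stated test

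*Protocol article*

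**What the plan says.** Three statements in the Sample size section bear on the complete response test.

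- The hypotheses: "The hypothesis that the proportion responding is 70% or more compared to the alternative hypothesis that 50% or fewer respond".
- The test: it "will be tested using a two sided binomial test with a target significance level of 0.10 and power of 0.80".
- The decision rule: "if 7 or fewer patients respond the trial will be terminated" after the first 15. Then: "If 8 or more patients respond, the trial may go to the second stage, recruiting a further 13 patients". Finally: "Of the total of 28 patients, 18 or more must respond to the treatment to be considered better than current treatment".

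The section on statistical methods for primary and secondary outcomes says that the complete response proportion will be "presented with 95% confidence intervals and compared to the hypothesized null effect of 0.5 using an exact binomial test". It gives no side for that test, and the paragraph opens by referring to the first stage.

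**The concern.** The decision rule points one way only: enough responders means better than current treatment, and no count leads to a claim of worse. That is a one-sided test with 50% as the null. The sentence before it calls the test two-sided and makes 70% the hypothesis under test, while the statistical methods section takes 0.5 as the null. These statements cannot all describe the same test.

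Complete response is a co-primary endpoint and the only efficacy criterion in the design. If a two-sided test at 0.10 and an 18/28 threshold both stand, a result on the threshold has two prespecified verdicts, and the choice between them could be made after the data are seen. The error rate would also be misdescribed: a two-sided 0.10 test implies about 0.05 in the upper tail, whereas the rule spends 0.09 there.

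**Working it through.** **Inputs**, all from the Sample size section: n1 = 15, stop if X1 ≤ 7; n = 28, success if the total is ≥ 18; rates 0.50 and 0.70; alpha 0.10; power 0.80. The null of 0.5 is confirmed by the statistical methods section.

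**1. Reproduce the design.** With X1 ~ Bin(15, p) and X2 ~ Bin(13, p),

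P(success | p) = Σ over x = 8 to 15 of P(X1 = x) · P(X2 ≥ 18 − x).

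- At p = 0.50: 0.0900. The chance of stopping after stage 1 is 0.50.
- At p = 0.70: 0.8009.

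An exhaustive search for the smallest maximum n with P(success | 0.50) ≤ 0.10 and P(success | 0.70) ≥ 0.80 returns exactly 15 / stop at ≤ 7 / 28 / success at ≥ 18. The printed numbers are therefore correct for H0 p ≤ 0.50 against H1 p ≥ 0.70 at one-sided alpha 0.10.

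**2. Apply the stated two-sided test at n = 28.** Against 0.5 the exact two-sided p is twice the upper tail.

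| Responders of 28 | One-sided p | Two-sided p | Rule | Two-sided test at 0.10 |
|---|---|---|---|---|
| 17 | 0.1725 | 0.345 | fail | not significant |
| 18 | 0.0925 | 0.185 | success | not significant |
| 19 | 0.0436 | 0.087 | success | significant |

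Allowing for the stage 1 stop, the one-sided p at 18/28 is 0.0900, the figure from step 1.

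**3. Power of the stated test.** Keep the stage 1 stop and require 19 or more of 28:

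- P(success | 0.50) = 0.0432, within an upper-tail limit of 0.05.
- P(success | 0.70) = 0.6802, against the stated 0.80.

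The same search at upper-tail 0.05 needs n = 37 (n1 = 23, stop at ≤ 12, success at ≥ 24; alpha 0.0482, power 0.801). The 28-patient design therefore cannot have come from a two-sided 0.10 calculation.

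**4. How often the two conflict.** They differ only at exactly 18. At p = 0.70 that has probability 0.8009 − 0.6802 = 0.1207, about 12%, if stage 2 always opens after 8 or more responders.

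**5. Sensitivity to the stage 1 boundary.** The abstract gives a different stage 1 stop (fewer than 7), which is a separate matter. With a stop at ≤ 6 the rule has alpha 0.0922 and power 0.8079; requiring 19 gives 0.0436 and 0.6824. The conclusion on sidedness is the same.

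**The case against.** The best defence is that the operative rule is explicit. The boundaries are fixed, point one way, and meet the stated targets of 0.10 and 0.80. On that view the two-sided label is a single misplaced phrase, the reversed hypotheses are a drafting slip, and nobody would be misled about what counts as success. The conflict is confined to one count, and reaching it needs a second stage that the protocol makes optional and subject to feasibility. Much of this stands: the sample size and boundaries are sound and the error is in the wording. It does not remove the contradiction, because the document states the test, its level and its power as well as the threshold, and no analysis plan could honour both.

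Three stronger readings are tempting and are not supported.

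- **The 95% interval as a further decision rule.** At 18/28 it runs from 0.441 to 0.814 and at 19/28 from 0.476 to 0.841, so both include 0.5. A reader might infer a conflict at both counts. The protocol only says that the interval will be presented, in a paragraph that opens with the first stage, and never makes exclusion of 0.5 a criterion.
- **A true significance level of 0.20.** Taking 70% as the real null would make the level 1 − 0.801 = 0.199. The stated aim of improving on chemoradiation, the null of 0.5 in the statistical methods and the success rule all show that 50% is the null. The inversion needs correcting but changes no error rate.
- **A trial that is too small.** The 37-patient figure applies only if a two-sided test was intended, and the boundaries show that it was not.

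**Conclusion.** The point holds. As written, the Sample size section attaches a two-sided label and reversed hypotheses to a design that is one-sided at 0.10 with 50% as the null. The stated power of 0.80 belongs to the 18/28 rule (0.801), not to a two-sided 0.10 test (0.680).

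The practical effect is narrow: one ambiguous outcome, exactly 18/28. The 12% probability rests on a true rate of 0.70 and on stage 2 always opening after 8 or more responders. If stage 2 is sometimes not opened, it is smaller. The two-sided p of 0.185 treats the 28 patients as a single-stage sample, as a plain exact binomial test does. Because the contradiction touches the significance level, the power and the success threshold of a co-primary endpoint, it should be settled before the final analysis, even though no design quantity is wrong.

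**What to change.** In the Sample size section, state H0 p ≤ 0.50 against H1 p ≥ 0.70, one-sided alpha 0.10 (attained 0.090), power 0.80, and name 18 or more of 28 as the sole final success criterion.

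In the statistical methods section, state that the exact test against 0.5 is one-sided and allows for the two stages (p = 0.090 at 18/28), and that the 95% confidence interval is descriptive.

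This is a change of wording only: sample size, boundaries and conduct are untouched. The small downside is that the protocol then declares an openly one-sided test at 0.10, which some readers will find lenient but which is what the design already is.

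### A stage-1 stop is to be reported as no more effective than standard treatment, but the stopping rule only screens against a 70% response rate and does not show a rate of 50% or lower

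*Protocol article*

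**What the plan says.** The Sample size section describes a two-stage minimax design that "requires an initial sample of 15 patients, with possibly an additional 13 patients required (total 28) subject to feasibility". The response rates are 50% and 70%, with a "two sided binomial test with a target significance level of 0.10 and power of 0.80". At stage 1, "if 7 or fewer patients respond the trial will be terminated" and "we will conclude that the treatment is not more effective than standard treatment". At the end, "Of the total of 28 patients, 18 or more must respond to the treatment to be considered better than current treatment".

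The Abstract (Methods) gives the stage-1 rule as: "If fewer than 7 patients achieved a complete response in the first stage, we will conclude the treatment is not more effective than standard treatment".

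Three other places bear on how that conclusion reads:

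- The section on the choice of comparators says that the study is single-arm and has none.
- The Background takes the 50% benchmark from the institution's own earlier prospective study of chemoradiation.
- The section on statistical methods for primary and secondary outcomes plans a 95% confidence interval for the complete response proportion and an exact binomial test against 0.5. It does not withdraw or qualify the conclusion fixed for a stage-1 stop.

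**The concern.** A two-stage futility rule answers one question: is the response so low that the target rate has become implausible and going on is not worthwhile? The plan attaches a different and stronger statement to the same event, namely that the regimen is no better than chemoradiation. That is a claim that the true rate is 50% or lower. Missing a boundary in 15 uncontrolled patients is not evidence for it.

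The Background states the hypothesis that adding durvalumab raises the complete response rate, so readers would take the fixed sentence as the answer to that hypothesis. A regimen with a real but moderate gain could then be reported as having none, next to a confidence interval that says otherwise.

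**Working it through.** **Inputs.** From the Sample size section: n1 = 15, n2 = 13, N = 28, stop at 7 or fewer, success at 18 or more, rates 0.50 and 0.70, level 0.10, power 0.80. From the Abstract: stop at fewer than 7, that is 6 or fewer. The Sample size section words its two hypotheses in reverse order. I take 0.50 as the null, as the statistical methods section does. The rates 55%, 60% and 65% are my assumptions for a moderate benefit, because the document gives only 50% and 70%.

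**1. The plan's own design.** P(success | p) = Σ over x = 8 to 15 of P(X1 = x | 15, p) × P(X2 ≥ 18 − x | 13, p).

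- At p = 0.50 this is 0.090 (one-sided).
- At p = 0.70 it is 0.801.
- A full search for the minimax design at one-sided 0.10 and power 0.80 returns these same numbers: 15, 7, 28, 18.

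The boundary and sample size reproduce, with the 0.10 met as a one-sided level.

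**2. How often stage 1 stops.** P(X ≤ r | 15, p) = Σ over x = 0 to r of C(15, x) p^x (1 − p)^(15 − x).

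| True rate | Stop at 7 or fewer (Sample size) | Stop at 6 or fewer (Abstract) |
|---|---|---|
| 50% | 0.500 | 0.304 |
| 55% | 0.347 | 0.182 |
| 60% | 0.213 | 0.095 |
| 65% | 0.113 | 0.042 |
| 70% | 0.050 | 0.015 |

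Under the Sample size rule, a stop is 0.500/0.050 = 10 times as probable at 50% as at 70%. It is only 0.500/0.213 = 2.3 times as probable at 50% as at 60%, and 0.500/0.347 = 1.4 times as probable as at 55%. The rule separates 50% from 70%. It hardly separates 50% from a moderate gain.

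**3. What a stopped trial would show.** The exact (Clopper-Pearson) 95% limits for x of 15 are the 0.025 quantile of Beta(x, 16 − x) and the 0.975 quantile of Beta(x + 1, 15 − x).

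| Responders | 95% interval |
|---|---|
| 7/15 | 21.3% to 73.4% |
| 6/15 | 16.3% to 67.7% |
| 5/15 | 11.8% to 61.6% |
| 4/15 | 7.8% to 55.1% |
| 3/15 | 4.3% to 48.1% |

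For 4 to 7 responders the interval includes rates above 50%. Only 3 or fewer excludes 50%. That is rare: at a true rate of 50%, P(X ≤ 3) = (1 + 15 + 105 + 455)/32768 = 0.018, which is 0.018/0.500 = 3.5% of all stops.

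**4. The disagreement at exactly 7.** The Sample size section stops the trial at 7 and the Abstract does not. The probability of exactly 7 is the difference between the two columns in step 2: 0.500 − 0.304 = 0.196 at 50%, 0.213 − 0.095 = 0.118 at 60%, and 0.050 − 0.015 = 0.035 at 70%.

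**The case against.** The strongest reply is that the sentence is phase II shorthand. It labels the decision not to reject a 50% benchmark within a two-hypothesis rule, the rule itself is correct, and no boundary, sample size or patient decision depends on the wording. In addition, the planned 95% interval would show any reader how uncertain 7 of 15 is. It is true that the rule is correct and that the interval is already planned. But the usual shorthand is that the regimen does not merit further study. The protocol goes on to a comparative efficacy statement, and printing the interval does not withdraw it.

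A reader might infer three stronger points, which the document does not support:

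- *That a moderately better regimen would usually be declared no better.* The chance of missing success overall is 61% at a true rate of 60%, 39% at 65% and 20% at 70%. However, the criticised conclusion attaches only to a stage-1 stop, which accounts for 21, 11 and 5 of those points. For 17 or fewer of 28 the protocol says only that the treatment does not meet the mark to be considered better, so the overall figures do not measure this fault.
- *That 15 patients could never support the conclusion.* With 3 or fewer responders the upper limit is 48%, so in that rare case they could.
- *That every stop leaves 70% plausible.* The 95% interval includes 70% only at 7 of 15. At the two-sided 90% level the upper limit for 7 of 15 is 70.0%, right at the target, and it is lower for smaller counts. A stop is real evidence against 70%.

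**Conclusion.** The point holds as a fault in the stated conclusion, not in the design. Following the text as written would produce an unsupported comparative claim after almost every stage-1 stop, namely at any count from 4 to 7. At assumed true rates of 55%, 60% and 65% that claim would be made, and would be false, in about 1 trial in 3, 1 in 5 and 1 in 9 under the Sample size rule. Under the Abstract's rule it would be 18%, 10% and 4%. These figures rest on exact binomial calculation, on the assumed moderate rates, and on taking 50% as the true rate for standard treatment, as the protocol does. The fault is minor, because it changes what is said and not how the trial is run. The conflict at exactly 7 responders is a separate inconsistency that needs settling in the same two sentences.

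**What to change.** Reword the conclusion in the Sample size section and in the Abstract along these lines: if the stage-1 boundary is not passed, the trial stops because the prespecified response level for continuing was not reached and the targeted 70% complete response rate is unlikely. The observed rate is interpreted with its 95% confidence interval, as already planned under statistical methods. No claim of no benefit over chemoradiation is made.

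In the same edit, reconcile the two stage-1 counts so that exactly 7 responders leads to one outcome throughout. With success at 18 of 28, both versions keep the one-sided level under 0.10 and the power above 0.80 (0.090 and 0.801 when stopping at 7 or fewer; 0.092 and 0.808 when stopping at 6 or fewer). The minimax search returns the first, which has the smaller expected sample size at 50% (21.5 against 24.1).

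The cost is two sentences and no extra patients. The downside is that a negative result will read less definitively.
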